## Abstract

**Background:**

The rate of lumbar fusion surgery (LFS) is increasing. Clinical recovery often lags technical outcome. Approximately 40 % of patients undergoing LFS rate themselves as symptomatically unchanged or worse following surgery. There is little research describing rehabilitation following LFS with no clear consensus as to what constitutes the optimum strategy. It is important to develop appropriate rehabilitation strategies to help patients manage pain and recover lost function following LFS.

**Methods/design:**

The study design is a randomised controlled feasibility trial exploring the feasibility of providing a complex multi-method rehabilitation intervention 3 months following LFS. The rehabilitation protocol that we have developed involves small participant groups of therapist led structured education utilising principles of cognitive behavioral therapy (CBT), progressive, individualised exercise and peer support. Participants will be randomly allocated to either usual care (UC) or the rehabilitation group (RG). We will recruit 50 subjects, planning to undergo LFS, over 30 months. Following LFS all participants will experience normal care for the first 3 months. Subsequent to a satisfactory 3 month surgical review they will commence their allocated post-operative treatment (RG or UC). Data collection will occur at baseline (pre-operatively), 3, 6 and 12 months post-operatively. Primary outcomes will include an assessment of feasibility factors (including recruitment and compliance). Secondary outcomes will evaluate the acceptability and characteristics of a limited cluster of quantitative measures including the Oswestry Disability Index (ODI) and an aggregated assessment of physical function (walking 50 yards, ascend/descend a flight of stairs). A nested qualitative study will evaluate participants’ experiences.

**Discussion:**

This study will evaluate the feasibility of providing complex, structured rehabilitation in small groups 3 months following technically successful LFS. We will identify strengths and weakness of the proposed protocol and the usefulness and characteristics of the planned outcome measures. This will help shape the development of rehabilitation strategies and inform future work aimed at evaluating clinical efficacy.

**Trial registration:**

ISRCTN60891364, 10/07/2014.

**Electronic supplementary material:**

The online version of this article (doi:10.1186/s13063-015-0751-9) contains supplementary material, which is available to authorized users.

## Background

Instrumented lumbar fusion surgery (LFS) is undertaken to rigidly stabilise adjacent vertebral motion segments, commonly performed simultaneously with decompression of affected neural tissue, to relieve back and/or neurogenic leg pain [1–3]. Common clinical indications include symptomatic disc disease, segmental instability, and spinal stenosis [4–6]. The rate of LFS is increasing in the UK with over 6,547 fusions performed in 2012/13 [7]. A similar trend of escalating LFS rates has been reported in the US [8].

Following instrumented LFS 15 % of patients show no improvement and as many as 40 % of patients are unsure/dissatisfied with the outcome 2 years postoperatively [9–12], reporting ongoing back pain and related limitation in daily function [13, 14]. Similar findings have been reported in surgery for lumbar spine stenosis where functional recovery lags behind surgical outcome, [15]. This adds to the already considerable burden of years lived with disability (YLD) as a consequence of low back pain (LBP) [16].

The financial implications are also significant. The direct costs of LFS utilising titanium cages is reported to be between £9,000 to £11,000 per case [9, 17]. In the US the cost per quality-adjusted life year (QUALY) has been estimated at £25,000 [18]. Overall costs at 2 years (direct and indirect), including lost productivity, are significantly higher at £78,000 [19]. In the UK National Health Service (NHS), surgery represents the greatest single expenditure in the management of chronic low back pain (CLBP) [6].

A recent report by the Cochrane Back Review Group (CBRG), concluded that active rehabilitation was more effective than usual care (UC) with respect to functional recovery following laminectomy for lumbar stenosis [20]. This suggests that rehabilitation can facilitate recovery from some forms of spinal surgery.

Few published studies have looked at rehabilitation following LFS. Christensen *et al.*, [21] showed rehabilitation involving directed exercise and a ‘back Café’ (peer support group) improved pain and function compared to UC. Similar results were reported by Abbot *et al.* [22], in which psychomotor therapy (home exercises and outpatient appointments targeting maladaptive pain cognition, behaviour and motor control exercises) significantly reduced disability and pain compared with a physical rehabilitation regime. Rehabilitation in this study [22] began immediately following surgery, which is not standard practice in many units. The issue of timing may be relevant, as rehabilitation commenced 6 weeks postoperatively has been associated with inferior outcomes when compared to that commenced at 3 months [23].

A recent systematic review reported inconclusive, very low quality evidence for the effectiveness of physiotherapy management following LFS [24]. This is largely due to the lack of good-quality studies, the authors identifying the two studies summarised above, as eligible for inclusion. However, both of these studies reported a positive effect in favour of complex rehabilitation over physical exercise [22] or UC [21]. This paucity in the literature represents a gap in our understanding as to what constitutes best practice for rehabilitation following LFS, echoed by others [25, 26]. Therefore, it is vital to develop strategies to improve outcomes both in terms of human function and cost following this operation.

### Aims and objectives

The aim of this study is to evaluate the feasibility of providing complex rehabilitation in a group setting 3 months after technically successful instrumented LFS. This will include an analysis of our recruitment strategy, compliance with the study protocol and rehabilitation intervention. It will also evaluate the acceptability and characteristics (including population mean, SD and effect size) of a cluster of quantitative outcome measures. This will help achieve a more detailed analysis of the patient group under evaluation and thus a robust basis for the analyses of future work evaluating clinical efficacy. The nested qualitative analysis will identify strengths and weakness of the proposed protocol. This study will provide useful data for the development, refinement, and analysis of complex rehabilitation following instrumented LFS.

## Methods

### Design of trial

Rehabilitation following fusion surgery (REFS) is a randomised, controlled, multi-method, single-centre, feasibility trial.

### Participants (inclusion and exclusion criteria)

A convenience sample of subjects (n = 50) will be recruited from the Neurosurgical Department of the National Hospital for Neurology and Neurosurgery, (NHNN, UCLH, NHS Foundation Trust). The Complex Spine Team at NHNN performs approximately 60 fusion procedures per annum. If 33 % of these patients are eligible and consent, we will meet our recruitment target in 30 months. A local exploratory study suggested this recruitment strategy is achievable; contingency plans are in place should recruitment prove inadequate. A study overview is shown in Fig. 1.

**Fig. 1 Fig1:**
[figure not shown]
Trial Flowchart. ^*^Quantitative data collection, Oswestry disability index (ODI), pain self-efficacy questionnaire (PSEQ), aggregated functional performance test (AFPT), hospital anxiety and depression score (HADS), Client Services Receipt Inventory (CSRI), (European quality of life questionnaire-5 dimensions (EQ-5D); ^∝^qualitative commentary data collection; ^β^detailed qualitative interviews data collection. RG, rehabilitation group; UC, usual care

Patients 18 to 75 years old will be included. Patients will be excluded if they have spinal cord involvement; have postoperative complications (infection, loosening or other technical failure of the surgical site that in the opinion of the attending surgeon precludes participation in rehabilitation); have had revision LFS (previous history of discectomy/decompression surgery are eligible); have lower limb joint pain that interferes with assessment or the ability to exercise; are unable to walk further than 20 m; have severe, poorly controlled psychological or physical comorbidity; have inadequate verbal and written English, or are unable/unwilling to undertake exercise, attend the postoperative programme or give signed consent.

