### Recruitment/consent

Potential participants will be identified from the neurosurgical waiting list by JG. All patients undergoing LFS undergo a pre-operative assessment (PAS) to establish fitness for surgery. When patients are contacted to arrange the PAS the Chief Investigator (CI) will raise the possibility of the study. Those agreeing to consider participation will be sent a patient information sheet (PIS) (Additional file 1). At the PAS the CI will discuss any aspects of the study that are unclear. Patients who agree to participate will be asked to provide written informed consent (Additional file 2) and baseline data (BLD). These will be recorded, the participant’s general practitioner (GP) will be informed and they will be randomised to either RG or UC by block randomisation.

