### Immediate postoperative care

Following LFS both groups will remain in hospital for approximately 5 days, experiencing identical care, including early ambulation, (usually within 6 h of the operation), check radiographs, wound monitoring, pain control, routine nursing observations, physiotherapy mobility check/advice and antithrombotic exercises.

The standard advice given to all patients following LFS in our unit is to avoid heavy lifting (nothing more than a kettle) for 3 months. This allows wound healing and encourages consolidation of the osseous fusion. During this period patients are encouraged to gradually increase their outdoor mobility with short regular walks to a maximum of 2 miles/day. All subjects will follow this standard advice for the first 3 months following surgery, irrespective of group allocation. A check appointment 6 weeks postoperatively with the surgical team monitors recovery.

At 3 months following surgery, if the surgical team is satisfied with the technical aspects of the surgery (no indication of infection, loosening of the metal ware, or unexpected symptomology) participants will commence treatment according to their randomisation group (RG or UC).

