### Primary and secondary outcome measures

Primary outcome measures include a range of markers evaluating the feasibility of the protocol, specifically the recruitment process, compliance and acceptability, as follows. For the recruitment process these will be the numbers of: eligible patients; patients who accept the PIS (following phone contact from the CI); patients willing to discuss trial participation (with the CI at PAS), and participants who provide consent and BLD. For compliance these will be: the rehabilitation intervention (review of exercise diaries and attendance); usual care (attendance at other rehabilitation settings/type of rehabilitation provided); the trial protocol, and the rate of/reasons for attrition. For the acceptability of the rehabilitation group and UC this will be qualitative evaluation to better understand participants’ perceptions of surgical after care in RG and UC.

The secondary evaluation utilises a cluster of quantitative outcome measures. The differences between groups will be investigated taking into account the variation between patients and the longitudinal nature of the data, using such methods as repeated measures analysis of variance (ANOVA) or multilevel regression as appropriate. The longitudinal approach will allow us to use all observations even if a patient is lost to follow up. The observed effect size and inter-patient variance will allow us to propose a suitable sample size for future research. The measures include: the Oswestry disability index (ODI), which measures self-reported level of disability [31]; the aggregated functional performance test (AFPT), which is the aggregated time (in seconds) for the subject to sit-to-stand, walk 50 yards, and make a stair ascent/descent, to quantify the level of physical function [32, 33]; the pain self-efficacy questionnaire (PSEQ), which measures self-reported ability to self-manage pain [34]; the hospital anxiety and depression scale (HADS), a measure of hospital-related level of anxiety and depression [35]; the European quality of life-5 dimensions (EQ-5D) measure of health-related quality of life across a range of indicators [29], and the client services receipt inventory (CSRI), an economic questionnaire customised to the patients’ needs post LFS [36].

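### Postoperative complications are listed as an exclusion criterion although participants are randomised before surgery, so applying it removes randomised participants and leaves the group comparison open to selection bias

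*Protocol article*

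**What the plan says.** **Order of events.** Under Recruitment/consent, the pre-operative assessment is where "Patients who agree to participate will be asked to provide written informed consent (Additional file 2) and baseline data (BLD"), after which "they will be randomised to either RG or UC by block randomisation". Immediate postoperative care confirms that allocation already exists after the operation: "All subjects will follow this standard advice for the first 3 months following surgery, irrespective of group allocation".

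**Exclusion.** Participants (inclusion and exclusion criteria) nevertheless excludes patients who "have postoperative complications (infection, loosening or other technical failure of the surgical site that in the opinion of the attending surgeon precludes participation"; what is meant is taking part in rehabilitation.

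**Three-month review.** Immediate postoperative care describes a review at 3 months, after which "participants will commence treatment according to their randomisation group (RG or UC"). This start is conditional, and the condition is worded as follows: "if the surgical team is satisfied with the technical aspects of the surgery (no indication of infection, loosening of the metal ware, or unexpected symptomology"). The section does not say what happens to a randomised participant who fails this review.

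**Population.** Aims and objectives concerns rehabilitation "3 months after technically successful instrumented LFS".

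**Outcomes.** Primary and secondary outcome measures makes recruitment counts, compliance and attrition (rate and reasons) primary. The quantitative group comparison is secondary, but its observed effect size is to inform a future sample size. On incomplete follow-up: "The longitudinal approach will allow us to use all observations even if a patient is lost to follow up".

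**Blinding.** Randomisation and blinding says that participants cannot be blinded. It says nothing about the surgeon.

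**The concern.** An eligibility criterion should be settled before allocation. This one can be settled only after surgery, up to about 3 months after allocation, so as an exclusion it can act only on people already randomised.

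Three features make that more than untidy:

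- The decision is a judgement about fitness for rehabilitation. Only RG has a scheduled programme to be judged fit for, so the same borderline recovery may be judged more strictly in one arm.
- The person judging is not stated to be unaware of allocation.
- The rule appears in two forms. The exclusion list requires a complication that rules out rehabilitation. The 3-month review also covers unexpected symptoms, which is broader. The two could remove different people.

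At stake are the RG-UC effect size carried forward to the next trial, and two primary feasibility figures (attrition and compliance) whose values depend on where review failures are placed.

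**Working it through.** **1. The plan's own figure.** From Participants: 60 procedures per year, 33% eligible and consenting, 30 months. 60 × 0.33 × 2.5 = 49.5, against 50 stated. The figure reproduces, and it leaves no allowance for losses at the 3-month review.

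**2. Will the case arise?** The article gives no complication rate, so let c be the share failing the review, assumed to lie between 2% and 20%. Expected failures among 50 are 50c. The chance of at least one is 1 − (1 − c)^50. To have 50 people pass the review, 50/(1 − c) must enter, which takes 12 × n/(60 × 0.33) months.

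| c (assumed) | Expected failures of 50 | P(at least one) | Entrants needed for 50 to pass | Months |
|---|---|---|---|---|
| 2% | 1 | 0.64 | 52 | 31.5 |
| 5% | 2.5 | 0.92 | 53 | 32.1 |
| 10% | 5 | 0.99 | 56 | 33.9 |
| 20% | 10 | >0.99 | 63 | 38.2 |

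**3. Attrition.** Assume a further 10% loss among those who pass. If review failures are left out, attrition is 10%. If they are counted, it is c + 0.10(1 − c):

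- c = 5%: 0.05 + 0.095 = 14.5%
- c = 10%: 0.10 + 0.09 = 19%
- c = 20%: 0.20 + 0.08 = 28%

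**4. Compliance denominator.** A participant who fails the review attends no session. A compliance rate x among RG starters becomes x(1 − c) among all randomised to RG, that is 0.9x at c = 10%.

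**5. Which recruitment counts are touched?** Accepting the information sheet, willingness to discuss, and consent with baseline data all occur before surgery and are fixed by then. The number eligible is also fixed if it means eligible as screened from the waiting list. It stays open until after surgery only if the full exclusion list is applied literally.

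**6. Possible bias in the comparison.** Let complications occur in a share q of each arm, let those patients score m SD worse, and let a share s of them be removed. With no treatment effect, the mean of those kept is q(1 − s)m/(1 − qs).

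- Same s in both arms: the expected difference is 0.
- All removed in RG, half in UC: from 0.05 × 0.5 × 0.5/0.975 = 0.01 SD (q = 5%, m = 0.5) to 0.20 × 0.5 × 1/0.90 = 0.11 SD (q = 20%, m = 1), favouring RG.
- All removed in RG, none in UC: qm, from 0.025 to 0.20 SD.

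Assuming 25 per arm, the standard error of the difference is √(2/25) = 0.28 SD. Every q, m and s here is an assumption; the document supplies none.

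**The case against.** Care before the review is the same in both arms and the review applies to both, so with even application the expected bias is zero. That stands. A reader might infer that the comparison is distorted. The text permits arm-dependent removal but does not establish it.

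A reader might also cite chance imbalance: with two arms of 25 and an assumed 10% failure rate, the arms differ by three or more failures with probability 0.23 (0.10 at 5%, 0.37 at 20%). That is chance variation, not bias.

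Exclusion may mean only not starting the allocated programme, which is how the review paragraph works. The article does not say that data are discarded. The sentence on using all observations concerns loss to follow-up. It is silent on exclusion, so it is not contradicted. Analysis sets are commonly left to a fuller document, and the trial flowchart is not shown. These points stand and limit the claim. They do not remove the incompatibility: the article itself fixes both an eligibility rule and a randomisation time at which the rule cannot be applied, and Recruitment/consent and Immediate postoperative care agree on the order.

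The commitment to report reasons for attrition would allow surgical failure to be separated from programme drop-out. This softens the attrition point, but the headline rate and the compliance denominator stay undefined.

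UC participants may also receive physiotherapy, so fitness for rehabilitation is not irrelevant to them. Still, only RG has a fixed programme.

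**Conclusion.** The concern holds in limited form. The exclusion criterion and the time of randomisation are incompatible as written, and the 3-month condition is worded in two different ways. The comparison is open to selection bias because the judgement follows allocation, is not stated to be made without knowledge of it, and bears mainly on one arm.

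The size of any bias cannot be derived from the document. Under the assumed scenarios of arm-dependent removal it ranges from 0.01 to 0.20 SD, below the 0.28 SD standard error at 25 per arm. The more concrete effect is on attrition, which could read as 10% or as 14.5% to 28% depending on the counting rule, given the assumed 5% to 20% review failure and 10% other loss.

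A reader might conclude that all the primary counts are compromised. They are not, since three of the four recruitment counts are fixed before surgery. This should be fixed, but it is not critical: the comparison is secondary, and the Discussion says the trial is not designed to show efficacy.

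**What to change.** Reconcile Participants, Recruitment/consent and Immediate postoperative care in one of two ways.

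**Option A: keep pre-operative randomisation.** Remove postoperative complications from the exclusion criteria and treat the 3-month review as a condition for starting allocated treatment. Follow every randomised participant to 12 months and analyse as allocated. Report review failures by arm, separately from later attrition, and give compliance over both all randomised and all starters. State whether whoever makes the review decision knows the allocation. This costs protocol wording and a row in the flow diagram.

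**Option B: randomise after the review.** Keep consent and baseline data pre-operative, and open the next envelope only once a satisfactory review is recorded. The criterion then precedes allocation, and earlier losses become a line in the recruitment flow. The cost is fewer than 50 randomised (50 × 0.90 = 45 at an assumed 10% failure), or 56 consented over about 34 months to randomise 50. RG organisers also get less notice of who will join.

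Under either option, the two wordings of the 3-month condition must be made to agree. Which wording is right is a clinical matter for the trial team. Trial status says that the first subjects are being recruited, so either change is still practicable. Option A also covers anyone already randomised before surgery.

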### Recruitment/consent

Potential participants will be identified from the neurosurgical waiting list by JG. All patients undergoing LFS undergo a pre-operative assessment (PAS) to establish fitness for surgery. When patients are contacted to arrange the PAS the Chief Investigator (CI) will raise the possibility of the study. Those agreeing to consider participation will be sent a patient information sheet (PIS) (Additional file 1). At the PAS the CI will discuss any aspects of the study that are unclear. Patients who agree to participate will be asked to provide written informed consent (Additional file 2) and baseline data (BLD). These will be recorded, the participant’s general practitioner (GP) will be informed and they will be randomised to either RG or UC by block randomisation.

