### Randomisation and blinding

It is not possible to blind subjects to their allocation. Randomisation to either RG or UC will be by block randomization, utilising codes generated independently by the trial statistician at the Faculty of Health and Social Care Sciences, St Georges University of London (HEI). Concealment of allocation will be achieved by the remote generation of codes and the use of sealed opaque envelopes, numbered sequentially.

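### A surgical exclusion criterion is applied up to 3 months after randomisation, so the arms compared could be a subset of the arms randomised and the attrition count is ambiguous

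*Protocol article*

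**What the plan says.** Under Recruitment/consent, everything up to allocation happens before surgery. "Patients who agree to participate will be asked to provide written informed consent (Additional file 2) and baseline data (BLD"), after which "they will be randomised to either RG or UC by block randomisation".

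Under Participants (inclusion and exclusion criteria), patients are excluded if they "have postoperative complications (infection, loosening or other technical failure of the surgical site that in the opinion of the attending surgeon precludes participation in rehabilitation").

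Under Immediate postoperative care, both arms receive the same care and advice for 3 months. Then: "At 3 months following surgery, if the surgical team is satisfied with the technical aspects of the surgery", "participants will commence treatment according to their randomisation group (RG or UC"). The Abstract has the same sequence: "Subsequent to a satisfactory 3 month surgical review they will commence their allocated post-operative treatment (RG or UC").

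On blinding, Randomisation and blinding states "It is not possible to blind subjects to their allocation". It says nothing either way about the surgical team.

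Primary and secondary outcome measures makes compliance and the rate of and reasons for attrition primary. It plans between-group comparisons of the Oswestry Disability Index (ODI), the functional performance test and other measures as secondary, and uses the observed effect size and variance to size a later trial. It undertakes to use all observations from patients lost to follow-up. It does not mention patients whom the surgical team does not clear.

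**The concern.** An exclusion criterion defines who enters a trial, so it has to be assessable before allocation. This one cannot be: it concerns complications of an operation that takes place after allocation. Two features make the timing matter.

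- **The question is not neutral between arms.** It asks whether a complication rules out rehabilitation. That has a direct consequence for someone allocated to RG and much less for someone allocated to UC. A borderline patient could be excluded from one arm and kept in the other.
- **It is a judgement, and no blinding of those who make it is described.**

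Two things are at stake. The first is the between-group effect size, which is meant to inform a later trial. If patients with a poor outlook are removed more often from RG, the estimate is tilted in favour of RG. The second is the primary attrition outcome. A participant who fails the review could be recorded as ineligible, and so leave the denominator, or as lost, and so count in the numerator. The document supports either reading.

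**Working it through.** **1. The plan's own figure.** About 60 procedures a year, 33% eligible and consenting, 30 months (Participants section):

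60 × 0.33 × 2.5 = 49.5, which reproduces the target of 50. The target counts people at consent. No allowance for losses before the 3-month review is stated.

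**2. How many might be lost.** The documents give no rate, so 5% to 20% is an assumption.

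| Assumed loss | Remaining of 50 | Randomised to keep 50 past the review | Months at 60 × 0.33 = 19.8 a year |
|---|---|---|---|
| 5% | 47.5 | 50/0.95 → 53 | 32.1 |
| 10% | 45 | 50/0.90 → 56 | 33.9 |
| 15% | 42.5 | 50/0.85 → 59 | 35.8 |
| 20% | 40 | 50/0.80 → 63 | 38.2 |

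**3. How large a bias could be.** Assume no true treatment effect, a normally distributed outcome in SD units, and an exclusion judgement that correlates ρ with outcome and removes the worst fraction q of an arm. The mean of those who remain shifts by

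ρ × φ(z)/(1 − q), where z is the (1 − q) quantile of the standard normal.

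At ρ = 1:
- q = 5%: 0.1031/0.95 = 0.109
- q = 10%: 0.1755/0.90 = 0.195
- q = 20%: 0.2800/0.80 = 0.350

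The spurious difference between arms is ρ × [shift(q in RG) − shift(q in UC)]:

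| Excluded RG / UC | ρ = 0.3 | ρ = 0.5 | ρ = 1.0 |
|---|---|---|---|
| 10% / 10% | 0 | 0 | 0 |
| 10% / 5% | 0.026 | 0.043 | 0.086 |
| 10% / 0% | 0.058 | 0.097 | 0.195 |
| 20% / 5% | 0.072 | 0.121 | 0.241 |

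All the non-zero entries favour RG.

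**4. Yardstick.** For a simple comparison with 25 per arm, the standard error of the standardised difference is √(2/25) = 0.283 SD.

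**5. Numbers of people.** In an arm of 25, 10% is 2.5 people and 5% is 1.25, so the unequal scenarios turn on one or a few individual judgements.

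**The case against.** The strongest reply is that the review applies to both arms after identical care. Complications themselves should therefore not depend on allocation, and the listed triggers (infection, loosening, technical failure) are largely physical findings. This stands. Bias requires a judgement, or a withdrawal, that differs by arm, and equal exclusion gives zero.

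Second, no sentence says that patients who fail the review leave follow-up or analysis. Immediate postoperative care speaks only of starting treatment, and an analysis plan or full protocol that is not shown could keep everyone in. A reader might infer that the arms compared will certainly not be the arms randomised; the documents do not support that. They do list the complication as an exclusion from the trial, and the undertaking to use all observations is worded for loss to follow-up. The conflict within the article therefore remains.

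Third, the trial is not designed to show efficacy, and losses between allocation and 3 months are part of what it sets out to measure. This stands and lowers the severity. It does not settle how a failed review is to be labelled.

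Other tempting inferences go beyond the text:
- That early allocation gains nothing. RG runs in groups of up to eight over 10 weeks, so lead time for scheduling may be useful.
- That participants give their 3-month measures knowing their arm. They cannot be blinded, but the article does not say when allocation is disclosed.
- That UC participants will withdraw in disappointment or seek rehabilitation early. The article offers no evidence for this, and outside rehabilitation is permitted and recorded.

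**Conclusion.** The point holds at moderate severity. Recruitment/consent, the exclusion criteria and Immediate postoperative care together apply an eligibility rule to people already randomised. The rule bears more on RG than on UC, and no blinding is described for those who apply it. Followed as written, it could reduce the compared set to a subset of the randomised set, and it makes the primary attrition count ambiguous.

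The size cannot be derived from the documents, which give no exclusion rate. The expected bias is zero if exclusion is equal. It is about 0.03 to 0.24 SD under the assumed splits of 10% v 5% to 20% v 5% with correlations of 0.3 to 1.0. That is below one standard error (0.28 SD), but its direction is systematic and it would carry into the effect size used to plan the next trial.

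A reader might take the one-arm figures of 0.11, 0.195 and 0.35 SD (5%, 10% and 20% removed from one arm, none from the other, perfect correlation) as the likely bias. They are an upper bound for those fractions, not an estimate, because the review applies to both arms.

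**What to change.** **For participants not yet allocated.** Keep identification, consent and baseline data at the pre-operative assessment. Open the next sealed envelope only after the 3-month surgical review has been passed and the 3-month measures have been recorded. The complication criterion then becomes a pre-randomisation screen. Report those consented but not randomised, with reasons, as a feasibility count.

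**For anyone already randomised before surgery, or for everyone if the timing is kept.** Remove postoperative complications from the criteria for exclusion from the trial, and treat a failed review only as a reason for not starting allocated care. Follow and analyse everyone in the arm to which they were randomised. Report failed reviews by arm, as a separate category within attrition. The surgical team's decision on who may start rehabilitation is unaffected.

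**Cost.** Later randomisation needs a protocol amendment and a change to the consent wording. Participants learn their allocation later, and there is less lead time to fill the groups. If consents stay at 50, about 40 to 47 are randomised at an assumed loss of 20% to 5%; keeping 50 randomised would take roughly 32 to 38 months instead of 30. The article does not say whether the surgical review and the 3-month measures share a visit, so whether an extra contact is needed must be checked. Trial status says the first subjects are being recruited, so few should have been allocated under the present timing, but the timing of randomisation must be reported for them. The second option needs only a change of wording and continued follow-up of those not cleared.
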